### 5.2.2. Conflicting recommendations for dose modification

A subject may simultaneously experience several clinically significant toxicities requiring dose modification. If the recommendations for dose modification related to the simultaneously experienced toxicities conflict with one another, the investigator should select the dose modification resulting in the lowest dose level.

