| Grade 3                      | Delay until $\leq$ Grade 2 a | Reduce by 1 dose level                                                                                | If toxicity remains $\leq$ Grade 2, dose re-escalation may be considered at the discretion of the treating investigator. If dose is re-escalated and toxicity ( $\geq$ Grade 3) recurs, institute permanent dose reduction |
| Grade 4                      | Delay until $\leq$ Grade 2 a | Reduce by 1 dose level. Permanent discontinuation may be considered at the investigator's discretion. | ---                                                                                                                                                                                                                        |

\* Excludes alopecia, non-refractory nausea/vomiting, non-refractory hypersensitivity, and non-clinically significant and asymptomatic laboratory abnormalities

a: If no recovery after one cycle (4 consecutive weeks; maximum of 5 weeks between doses of regorafenib), treatment should be permanently discontinued.

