#### 3. Cushions

Protect tender areas:

- Use socks/gloves to cover moisturizing creams.
- Wear well-padded footwear.
- Use insole cushions or inserts (eg, silicon, gel).
- Foot soaks with tepid water and Epsom salts

If supportive measures do not produce the desired effects, dose modification, as outlined in Table 3, is the next step. Dose interruption (7 days) followed by

restarting treatment at Dose Level -1 may be instituted for Grade 2 toxicity if supportive measures do not reduce the severity to  $\leq$  Grade 1 within 7 days.

For subjects with Grade 3 HFSR, at the first occurrence a 1-level dose reduction is recommended; at the second occurrence a decrease of an additional dose level is recommended.

Study treatment is to be discontinued for the fourth occurrence of HFSR Grade 2 and for the third occurrence of HFSR Grade 3.

For subjects who require a dose reduction for Grade 2 or 3 HFSR, the dose of study drug may be increased to the starting dose after one full cycle of therapy has been administered at the reduced dose without the appearance of HFSR  $>$  Grade 1. Dose escalation should be done one dose level at a time.

In general, a more liberal management for dose modification is allowed if judged by the investigator to be medically appropriate (eg, dose reduction for Grade 1 HFSR).

**Table 3: Dose modification/interruption and toxicity grading for hand-foot skin reaction (palmar-plantar erythrodysesthesia syndrome)**

| Skin Toxicity Grade (CTCAE v 4.0)                                                                                                                                            | Occurrence                                 | Suggested Dose Modification/Interruption a                                                                                                                    |
|------------------------------------------------------------------------------------------------------------------------------------------------------------------------------|--------------------------------------------|--------------------------------------------------------------------------------------------------------------------------------------------------------------------------|

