| Grade 1: Numbness, dysesthesia, paraesthesia, tingling, painless swelling, erythema or discomfort of the hands or feet that does not disrupt the subject's normal activities | Any                                        | Maintain dose level and institute supportive measures immediately for symptomatic relief.                                                                                |
| Grade 2: Painful erythema and swelling of the hands or feet and/or discomfort that affects the subject's normal activities                                                   | 1st occurrence                             | Institute supportive measures immediately. Consider decreasing dose by one dose level; if no improvement, interrupt therapy for 7 days or until toxicity $\leq$ Grade 1. |
|                                                                                                                                                                              | No improvement at 7 days or 2nd occurrence | Interrupt therapy $\leq$ 28 days a or until toxicity $\leq$ Grade 1. When resuming treatment, reduce dose by one dose level.                                  |
|                                                                                                                                                                              | 3rd occurrence                             | Interrupt therapy $\leq$ 28 days a or until toxicity $\leq$ Grade 1. When resuming treatment, reduce dose by one additional dose level. b,c        |
|                                                                                                                                                                              | 4th occurrence                             | Discontinue treatment                                                                                                                                                    |

**Table 3: Dose modification/interruption and toxicity grading for hand-foot skin reaction (palmar-plantar erythrodysesthesia syndrome)**

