| AST and/or ALT $\leq 5 \times \text{ULN}$ ( $< \text{Grade } 3$ )                                                   | Continue dosing, with weekly monitoring of liver function until transaminases return to $< 3 \times \text{ULN}$ ( $\leq \text{Grade } 1$ ) or baseline.                                                                                              |                                                                                                                                                                                              |                   |
| ALT and/or AST $> 5 \times \text{ULN}$ ( $\geq \text{Grade } 3$ )                                                   | Interrupt dosing, with weekly monitoring until transaminases return to $< 3 \times \text{ULN}$ or baseline.                                                                                                                                          | If the potential benefit for reinitiating regorafenib is considered to outweigh the risk of hepatotoxicity: reduce 1 dose level and measure serum transaminases weekly for at least 4 weeks. | Discontinue.      |
| ALT and/or AST $> 20 \times \text{ULN}$ ( $\geq \text{Grade } 4$ )                                                  | Discontinue.                                                                                                                                                                                                                                         |                                                                                                                                                                                              |                   |
| ALT and/or AST $> 3 \times \text{ULN}$ ( $\geq \text{Grade } 2$ ) with concurrent bilirubin $> 2 \times \text{ULN}$ | Discontinue treatment and measure serum transaminases weekly until resolution.
Exception: subjects with Gilbert's syndrome who develop elevated transaminases should be managed as per the recommendations outlined above for ALT/AST elevations. |                                                                                                                                                                                              |                   |

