| Grade 2                     | SBP 140-159 mmHg or
DBP 90-99 mmHg
OR
Symptomatic increase in DBP >20 mmHg or to >140/90 mmHg if previously within normal limits | Treat with the aim to achieve DBP ≤ 90 mmHg.
If S/DBP previously within normal limits, start antihypertensive monotherapy.
If subject is taking antihypertensive medication, titrate the dosage up.  | Continue study drug.
If symptomatic, delay dose until symptoms resolve AND diastolic BP ≤ 90 mmHg. a
Restart dose at same dose level.                                                                                                                                                                                                       |
| Grade 3                     | SBP ≥ 160 mmHg or
DBP ≥ 100 mmHg
OR
≥1 antihypertensive drug or more intensive antihypertensive therapy required than previously | Treat to DBP ≤ 90 mmHg.
Start antihypertensive medication.
AND/OR
Increase dose of current antihypertensive medication.
AND/OR
Add additional antihypertensive medication(s). | Delay dose until DBP ≤ 90 mmHg and, if symptomatic, until symptoms resolve. a
Restart dose at same dose level.
If BP not controlled with more intensive therapy, reduce dose to Dose Level -1. b
If Grade 3 hypertension recurs after dose reduction and antihypertensive therapy, reduce dose to Dose Level -2. c |
| Grade 4                     | Life-threatening consequences (malignant hypertension):
transient or permanent neurologic deficit, hypertensive crisis                        | —                                                                                                                                                                                                          | Discontinue therapy.                                                                                                                                                                                                                                                                                                                                         |

In cases in which only one value is >Grade 1 (eg, 155/88 mmHg), the guidelines provided for the highest grade should be followed.

BP = blood pressure, DBP = diastolic blood pressure, SBP = systolic blood pressure.

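### For Grade 3 hypertension, Table 5 sets fixed dose targets, so a patient already on 120 mg gets no reduction at the first step

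*Protocol*

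**What the plan says.** Protocol Table 1 (section 5.2) defines three daily doses: Level 0 = 160 mg, Level -1 = 120 mg and Level -2 = 80 mg.

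The Grade 3 row of Table 5 (section 5.2.8) first holds regorafenib until diastolic pressure is 90 mmHg or lower and any symptoms have gone, and then says "Restart dose at same dose level". Two reduction steps follow:

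- First step: "If BP not controlled with more intensive therapy, reduce dose to Dose Level -1".
- Second step: "If Grade 3 hypertension recurs after dose reduction and antihypertensive therapy, reduce dose to Dose Level -2".

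The other tables describe a reduction relative to the dose the patient is on:

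- Table 2 (section 5.2.5), Grade 3: "Reduce by 1 dose level".
- Table 3 (section 5.2.6), Grade 2 hand-foot skin reaction without improvement at 7 days or at the second occurrence: "When resuming treatment, reduce dose by one dose level".
- Table 4 (section 5.2.7), on restart after a transaminase rise: "reduce 1 dose level and measure serum transaminases weekly for at least 4 weeks".

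**The concern.** The two steps in Table 5 name a destination, not a distance. They make sense only for a patient who is at Level 0 when the hypertension appears. A patient can properly be at Level -1 by then. Re-escalation under section 5.2.3 is discretionary and comes after a full cycle, and section 5.2.5 makes some reductions permanent. For that patient the first reduction step repeats the instruction before it, to restart at the same level.

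The first step is meant to lower the dose when stronger antihypertensive treatment has not been enough. Followed literally, it fails in a patient who has already shown reduced tolerance. With 5 to 10 centres planned, some investigators may follow the text and others the probable intention, and their patients would restart on different doses.

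**Working it through.** **Inputs.** Dose levels from Table 1: 4, 3 and 2 tablets of 40 mg, that is 160, 120 and 80 mg. Dosing days per cycle from section 5.1: 3 weeks of 4, that is 21 days.

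**Dose after the first reduction step, by starting level.**

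| Starting dose | Table 5 as written (target 120 mg) | One-level step |
|---|---|---|
| 160 mg (Level 0) | 120 mg | 120 mg |
| 120 mg (Level -1) | 120 mg | 80 mg |
| 80 mg (Level -2) | 120 mg, above the current dose | below the floor, so discontinue |

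The two rules agree only in the first line. The third line is an oddity of the wording more than a practical risk, because section 5.2, section 5.3 and the Table 5 footnotes already direct a patient who needs less than 80 mg to stop.

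**Size at Level -1.** Per day: 120 - 80 = 40 mg. Per cycle with all 21 doses taken: 120 × 21 = 2520 mg (63 tablets) against 80 × 21 = 1680 mg (42 tablets), a difference of 840 mg (21 tablets).

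**At recurrence.** Table 5 then moves the patient to 80 mg, the dose that a one-level step would already have reached.

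**Does another rule repair it?**

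- Section 5.2.2 selects the lowest dose level, but its condition is "If the recommendations for dose modification related to the simultaneously experienced toxicities conflict with one another". An earlier toxicity that has resolved does not meet it.
- Table 2 excludes hypertension by its title, so it cannot serve as a fallback.
- The floor rules concern doses below 80 mg and do not address a patient on 120 mg.
- The second step of Table 5 needs Grade 3 hypertension to recur. Pressure that is not controlled is a separate, earlier trigger.

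**Is it shorthand?** Probably. The text of section 5.2.6 says "restarting treatment at Dose Level -1 may be instituted for Grade 2 toxicity" for hand-foot skin reaction, where Table 3 steps down one level. The same slip from a relative to a fixed level therefore occurs elsewhere in the dose rules.

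**The case against.** The strongest reply is that the text does not force anyone to keep the patient on 120 mg. Section 5.2.4 presents the hypertension rules as recommended and uses the word required only for transaminase rises. An investigator may choose 80 mg, a predefined level, or may stop treatment under section 5.3. On this view the row is merely silent about a patient at Level -1, and its intention is easy to guess.

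The consequence is also bounded. No drug is given while diastolic pressure stays above 90 mmHg, a delay of more than one cycle ends treatment, and recurrence leads to 80 mg. Nor is the contrast with the other tables perfectly clean: Table 4 reduces only if the investigator decides to reinitiate, Table 3 only suggests considering a reduction at the first Grade 2 occurrence, and hypertension is deliberately handled more mildly, with antihypertensive treatment first.

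Most of this stands and limits the weight of the point. It does not remove it. An easily guessed intention means that the words do not say what was meant. The hold is also not a complete safeguard, because it is released on diastolic pressure and symptoms, whereas a systolic pressure of 160 mmHg or more is Grade 3 by itself. An asymptomatic patient at 165/88 mmHg is Grade 3 and already meets the restart condition. For that patient the reduction step is the main study-drug safeguard left in the row, and at Level -1 it does nothing.

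**Conclusion.** The point holds. As written, the first reduction step for Grade 3 hypertension lowers the dose by 0 mg in a patient already on 120 mg, where a one-level step would lower it by 40 mg per day (840 mg per full cycle). This rests on a literal reading of Table 5 and on the patient having stayed at Level -1 after an earlier toxicity, which the protocol allows. The per-cycle figure also assumes that all 21 doses are taken.

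How many patients this would affect is unknown, since the protocol gives no frequency for the sequence. The effect is confined to the restart dose of such patients. Sample size, error rates and the primary analysis are not involved. It is a drafting point with a safety purpose, and correcting it is optional.

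**What to change.** Reword the Grade 3 row of Table 5 along these lines: if pressure is not controlled despite intensified treatment, reduce by 1 dose level; if Grade 3 hypertension recurs after dose reduction and antihypertensive treatment, reduce by 1 additional dose level; if the patient is already at Dose Level -2, discontinue. In the same edit, replace the fixed level in the hand-foot skin reaction text of section 5.2.6 with a one-level step, as in Table 3.

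Patients at Level 0 are managed exactly as now, and the 80 mg floor is kept. The cost is one table row and one phrase at the next amendment, with no new procedure and no change to the design, sample size or endpoints.

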### 5.3. Definitive interruption of study treatment

A subject can definitively interrupt study treatment for the following reasons:

- Unequivocal progression of disease as demonstrated on a CT/MRI scan. In the case of equivocal lesions, subjects should continue to receive study drug until progression is confirmed (CT/MRI scan, follow-up).
- If, in the investigator's opinion, continuation in the study would be harmful to the subject's well-being
- At his/her own request or at the request of his/her legally acceptable representative. At any time during study treatment and without giving a reason, a subject or his/her legally acceptable representative may decline further study treatment. The subject will not suffer any disadvantage as a result. The subject will continue to be followed up for safety and survival unless he/she withdraws consent.
- Study drug dose reduction by more than two dose levels
- Study drug dose interruption for more than one cycle (4 consecutive weeks; maximum of 5 weeks between doses of regorafenib)
- Severe allergic reactions, such as exfoliate erythroderma, anaphylaxis, or vascular collapse
- Any other adverse reaction deemed sufficiently serious to warrant discontinuation of treatment by the investigator
- If female, a pregnancy test result consistent with pregnancy
- Use of illicit drugs or other substances that may, in the opinion of the investigator, have a reasonable chance of contributing to toxicity or otherwise confounding the results of the study
- Development of any intercurrent illness or situation that may, in the judgment of the investigator affect assessments of clinical status and study endpoints to a relevant degree
- Development of a second malignancy except for cervical cancer in situ, nonmelanoma skin cancer, or superficial bladder tumors classified as noninvasive tumor (Ta), carcinoma in situ (Tis), or tumor invades lamina propria (T1).
- Any subject who definitively interrupt study treatment will be evaluated at the End-of-treatment Visit conducted 30 days ( $\pm 7$  days) after permanently stopping study treatment.
- In all cases, the reason for definitive interruption of study treatment must be entered in the electronic Case Report Form (eCRF) and in the subject's medical records.

### 5.4. Drug logistics and accountability

Regorafenib will be stored at the investigational sites according to current laws. The coordinating center will manage drug accountability (including distribution, reception, return and distruction) according to the Standard Operating Procedures of the Clinical trials Unit at the National Cancer Institute of Napoli. All the data on drug accountability will be made available for audit or inspection by the drug manufacturer.

The investigators responsibility is to control the distribution to the patients and the use of the study drug. Study drug accountability must be performed for each cycle. Bottles must be returned to the investigator with all unused medication. Throughout the study, all unused study medication will be accounted for. The information on the number of tablets returned at each cycle will be collected through the electronic CRF. The reason(s) for any dose delay, reduction, or interruption also will be recorded in the CRF.

## 5.5. Concomitant treatment

### 5.5.1 Prior and concomitant therapy

All medication which is considered necessary for the subject's welfare, and which is not expected to interfere with the evaluation of the study drug, may be given at the discretion of the Investigator. All medications used during the study must be recorded in the subject's source documentation and in the CRF (including start/stop dates, dose frequency, route of administration, and indication). Disease-specific anti-neoplastic therapies, including kinase inhibitors, chemotherapy, radiation therapy, or surgical intervention, are not allowed during study treatment.

### 5.5.2. Inhibitors / inducers of CYP3A4

In vitro data indicate that regorafenib is metabolized by cytochrome CYP3A4 and uridine diphosphate glucuronosyl transferase UGT1A9.

Administration of ketoconazole (400 mg for 18 days), a strong CYP3A4 inhibitor, with a single dose of regorafenib (160 mg on Day 5) resulted in an increase in mean exposure (area under the curve, AUC) of regorafenib of approximately 33%, and a decrease in mean exposure of the active metabolites, M-2 (N-oxide) and M-5 (N-oxide and N-desmethyl), of approximately 90%.

Administration of rifampicin (600 mg for 9 days), a strong CYP3A4 inducer, with a single dose of regorafenib (160 mg on Day 7) resulted in a reduction in mean exposure (AUC) of regorafenib of approximately 50%, a 3- to 4-fold increase in mean exposure of the active metabolite M-5, and no change in exposure of active metabolite M-2. Other strong CYP3A4 inducers (eg, phenytoin, carbamazepine, phenobarbital, and St. John's Wort) may also increase metabolism of regorafenib.

Subjects on strong CYP3A4 inhibitors or inducers are not eligible for the study (see Section 5.2). During the study, strong CYP3A4 inhibitors (eg, clarithromycin, indinavir, itraconazole, ketoconazole, nefazodone, nelfinavir, posaconazole, ritonavir, saquinavir, telithromycin, voriconazole) or strong CYP3A4 inducers (eg, carbamazepine, phenobarbital, phenytoin, rifampin, St. John's Wort) are not permitted. A listing of CYP3A4 inhibitors and inducers is presented in Appendix.

### 5.5.3. UGT1A1 and UGT1A9 substrates

In vitro data indicate that regorafenib, as well as its active metabolites M-2, inhibits glucuronidation mediated by uridine diphosphate glucuronosyl transferases UGT1A1 and UGT1A9, whereas M-5 only inhibits UGT1A1 at concentrations that are achieved in vivo at steady state. Administration of regorafenib with a 5-day break prior to administration of irinotecan resulted in an increase of approximately 44% in mean exposure (AUC) of SN-38, a substrate of UGT1A1 and an active metabolite of irinotecan. An increase in mean exposure (AUC) of irinotecan of approximately 28% was also observed. This indicates that co-administration of regorafenib may increase systemic exposure to UGT1A1 and UGT1A9 substrates.

### 5.5.4. Breast cancer resistance protein and P-glycoprotein substrates

In vitro data indicate that regorafenib is an inhibitor of breast cancer resistance protein (BCRP) (median inhibition concentration [concentration that reduces the effect by 50%, IC50] values about 40 to 70 nanomolar) and P-glycoprotein (IC50 value of about 2 micromolar).

Co-administration of regorafenib may increase the plasma concentrations of concomitant BCRP substrates, such as methotrexate, fluvastatin, atorvastatin and rosuvastatin. Therefore, it is recommended to monitor patients closely for signs and symptoms of increased exposure to BCRP substrates.

Clinical data indicate that regorafenib has no effect on pharmacokinetics of digoxin, a P-glycoprotein substrate, therefore regorafenib can be given concomitantly with p-glycoprotein substrates, such as digoxin, without a clinically meaningful drug interaction.

